### Ethical Considerations

The study received ethical approval from the UCC’s Social Research Ethics Committee (ID 2022-027A1). The approval obtained from UCC sufficed as ethics coverage for the University of Galway in Ireland. Ethics approval was also received by the Mzuzu University Research Ethics Committee (ID MZUNIREC/DOR/23/28) and by the Inter-Faculty Research Ethics Committee at the University of Fort Hare (ID CIL002-21) in South Africa. The study will conform with the precepts of the Declaration of Helsinki on Human Rights of 1975. This research will involve participation through remotely answering survey questions and listening to podcasts. The survey is available in the English language only, as it is the official language in Ireland, Malawi, and South Africa. Participation in this research is not likely to cause any harm or pose a risk to the study participants’ well-being.

Informed consent will be explicitly sought from the study participants at the beginning of the survey, and participants are required to be 18 years of age and older. Only undergraduate nurses can take part in this research. Participate confidentiality will be upheld throughout the study process. To maintain confidentiality, no emails, names, or contact information will be required.

The study data will be stored on a password-protected laptop to which only the research team will have access. Participation in this study is entirely voluntary, and participants retain the right to withdraw their participation and data at any time while filling out the survey. However, once the survey is submitted, participants cannot withdraw because the survey is anonymous, and we can therefore not identify who completed the survey. Participants will not receive remuneration or compensation for taking part in the study.

## Results

Data collection is currently being conducted and will be carried out until February 2024. The quantitative and qualitative data are expected to be analyzed by March 2024.

## Discussion

### Comparison With Prior Work

This study, to the best of our knowledge, is the first podcast intervention study to compare the impact of podcasting on nursing education internationally. This is extremely pertinent considering the changing landscape of third-level education, the impact of web learning, and the shift away from conventional approaches [32]. This study may highlight the idea that the next generation may be keener on using this technology, as they have grown up with e-learning and internet-based content.

The implementation of podcasting in nursing education is a strategy that has been considered in previous literature. O'Connor et al [33] (2020) identified that the next generation of nursing students has grown up with technology and thus are mostly learners with diverse digital literacy abilities and perhaps a need for interactive, learner-centred courses. Fortunately, podcasting is emerging as a viable educational option. Abate [34] (2013) demonstrated that when undergraduate nursing students listened to a segmented podcast, they had increased scores on multiple choice exams and case study tests, compared to face-to-face lectures and unsegmented podcasts. Likewise, Burke and Cody [35] (2014) reported that 86% of undergraduate nursing students felt that podcasts enriched their learning, and an astonishing 94% of these students would recommend podcasting for other courses.

### Expected Findings

This study will investigate the impact of informational podcasts on the attainment of knowledge and awareness in undergraduate nursing students. It will provide valuable insights into the impact of podcasts in education settings across different countries. We anticipate that results from this study could illuminate whether educational podcasts serve as an impactful learning resource for undergraduate nursing students.

### Future Research

Other populations apart from undergraduate general nursing students should be included in further studies to determine the appropriateness of this intervention across third-level education. If the results are positive, this feasibility study will be used to inform future research on podcasting in third-level education.

### Strengths and Limitations

The role of social media platforms as a medium to deliver education has been under development for several years. This research will provide a clear contribution focusing on the impact of one such platform—YouTube—for undergraduate nursing students in the areas of knowledge and awareness on a set of given topics. This research is international and will enable a greater understanding of the usefulness of podcasts in a high-income country (Ireland) compared to middle-to-low-income countries (South Africa and Malawi). Nonresponse is one of the limitations of this study. Pre- and postpodcast questionnaires are planned to be administered before and after listening to a podcast recording. This may cause participants to become mentally fatigued and not fill out the questionnaire following the podcast, resulting in a reduced response rate. Another limitation of this study is selection bias. For this study, only general undergraduate nursing students will be used to gather information, and thus, they could skew the results due to the level of knowledge they should already have from their undergraduate studies. The generalisability of the study may be limited by the cohort only being composed of nursing students.

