**Methods:**

Pre- and postpodcast questionnaires will gather data regarding the participants’ knowledge and awareness of two topics—gestational diabetes and mental health. This intervention will be tested on general nursing undergraduate students. The total number of students (N=2395) from the participating universities are broken down as follows: (1) University College Cork (n=850) and the University of Galway (n=450) in Ireland, (2) Mzuzu University in Malawi (n=719), and (3) University of Fort Hare in South Africa (n=376).

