### Study Population

The study will collect data from undergraduate general nursing students from 4 universities located across Ireland, South Africa, and Malawi.

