### Inclusion and Exclusion Criteria

Exclusion criteria include those who are unable to complete the web-based questionnaires due to a lack of internet connection. These surveys are solely available via Google Forms and are thus inaccessible without an internet connection. Participants will be excluded if they are not a current resident and a registered undergraduate general nursing student of Ireland, South Africa, or Malawi and do not agree to consent to the study. As this is a feasibility study, we are targeting a small cohort of individuals who are convenient to the research team. Inclusion criteria encompass those aged 18 years and older.

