### Data Analysis

Microsoft Excel and Google Forms will be used to capture raw quantitative data and to execute the descriptive statistics in the form of percentages and frequencies. Descriptive statistics, including percentages, means, and standard deviations will be calculated for participants’ survey responses. For the pre- and posttest analysis, a paired 2-tailed *t* test analysis for the questions that assess medical knowledge will be performed. The means of both the pre and posttests will be calculated. The pretest will act as the control, and therefore, *P* values will be determined to identify if the results are statistically significant. This analysis will enable the observation of whether the podcasts were an effective intervention tool by examining a higher posttest mean score. Significance will be defined as *P*<.05.

This is an international feasibility study, and it would be of great interest to analyze participants’ country of residence in conjunction with the level of knowledge and awareness gained from the podcast to give us an insight into which country would benefit most from this form of audio learning. To conduct this, we will perform a subgroup analysis in SPSS. Furthermore, men and women have been shown to learn differently, with women preferentially being auditory learners [29]. Therefore, a subgroup analysis on gender will be carried out on SPSS. This research will help to clarify whether podcasting is a useful educational resource that is of benefit to both sexes as an alternative source of learning [30].

For this study, we only have 1 open-ended question, which is “Do you have any further comments on the podcast (duration or formatting), questions asked, or recommendations for future podcasts?” We will conduct a thematic analysis of the responses to open-ended questions [31]. To analyze and describe the comments, a coding frame will be developed. If responses contain 2 or more different statements, these statements or sentences will be coded separately or line by line.

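### Malawi and South Africa are each one university and Ireland is the only high-income country, so the country and income comparison cannot be separated from differences between universities

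*Protocol article*

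**What the plan says.** Under Study Population, the article draws on "undergraduate general nursing students from 4 universities located across Ireland, South Africa, and Malawi". The abstract gives the student numbers: "University College Cork (n=850) and the University of Galway (n=450) in Ireland", then 719 at Mzuzu University in Malawi and 376 at the University of Fort Hare in South Africa.

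Country is a stated target of inference in three places:

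- Objective of the Feasibility Study: research question 2 asks whether knowledge attainment differs between the three countries.
- Data Analysis: a subgroup analysis by country is planned, to "give us an insight into which country would benefit most from this form of audio learning".
- Strengths and Limitations: the research is said to "enable a greater understanding of the usefulness of podcasts in a high-income country (Ireland) compared to middle-to-low-income countries (South Africa and Malawi").

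The Introduction and Conclusions use the same framing, labelling Ireland high-income, South Africa upper-middle-income and Malawi low-to-middle-income.

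Inclusion and Exclusion Criteria describes a small cohort chosen for convenience to the research team and adds: "Exclusion criteria include those who are unable to complete the web-based questionnaires due to a lack of internet connection". Data Collection and Management states that university and year of study are recorded for each participant. The limitations listed are non-response, selection bias (explained only by nursing students' prior knowledge) and a cohort made up solely of nursing students.

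**The concern.** Where a country contributes one university, that university's curriculum, its teaching on gestational diabetes and mental health, and its way of inviting students are all part of the country result. If gain at Mzuzu differs from gain in Ireland, the data cannot say whether this reflects Malawi, a lower-income setting or Mzuzu itself. Following the plan as written would still produce a statement about which country benefits most, and the article's income framing invites a further step to income level. The listed limitations warn the reader of neither. What is at stake is the interpretation of research question 2 and of the international comparison that the article presents as its novelty.

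**Working it through.** **Inputs from the article.** Cork 850, Galway 450, Mzuzu 719, Fort Hare 376 (abstract, Methods). The stated total reproduces: 850 + 450 + 719 + 376 = 2395. This counts the students available; it is not a powered sample size, and there is no power figure to check.

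**What can be estimated.** Take the four universities as rows, with an intercept and indicators for country and university.

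- Country alone has rank 3.
- Country plus university has rank 4.
- University within country therefore has 4 − 3 = 1 degree of freedom, from Cork versus Galway only.
- The Malawi column equals the Mzuzu column, and the South Africa column equals the Fort Hare column. A university term adds nothing for either country.
- Judged against that 1 degree of freedom, the two-sided 5% critical t is 12.7. Grouping South Africa and Malawi as exchangeable gives at most 2 (critical t 4.30), but this merges their country and university differences.
- On the article's three income labels, each level holds one country. On its two-way split, the high-income group is Ireland alone. Either way, income level cannot be separated from country.

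This result needs no assumption.

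**Illustration 1: precision.** All of the following are assumptions: student SD of the gain 4 items (of the 27 gestational diabetes knowledge items), 10% response (130 in Ireland, 72 at Mzuzu), and between-university SD s of 0.5 to 1.5 items, with the two Irish universities weighted equally.

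- Student-only SE for Ireland versus Malawi: 4 × √(1/130 + 1/72) = 0.59.
- Between-university SE: s × √(1/2 + 1) = 1.22 s, which more replies do not reduce.
- Combined SE: √(0.59² + (1.22 s)²).

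| s (items) | Between-university SE | Combined SE | Student-only ÷ combined |
|---|---|---|---|
| 0.5 | 0.61 | 0.85 | 0.69 |
| 1.0 | 1.22 | 1.36 | 0.43 |
| 1.5 | 1.84 | 1.93 | 0.30 |

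**Illustration 2: false country differences.** Suppose there is no country effect and Ireland is compared with South Africa plus Malawi at student level, at nominal 5%. The false-positive rate is 2 × (1 − Φ(1.96 × √(V_naive/V_true))), where V_true adds the between-university variance weighted by squared university shares. With total variance set to 1, an assumed ICC of 0.01 and 10% response (130 versus 109.5):

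- V_naive = 0.99 × (1/130 + 1/109.5) = 0.0167.
- Sum of squared shares: (850/1300)² + (450/1300)² + (719/1095)² + (376/1095)² = 1.096.
- V_true = 0.0167 + 0.01 × 1.096 = 0.0276.
- False-positive rate: 13%.

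At an assumed ICC of 0.10 and full response, the same formula gives 82%.

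**The case against.** The best reply is proportion. Sampling and Sample Sizes gives the main aim as the paired pre/post comparison, which compares each student with himself or herself and is untouched. Country is a subgroup question in a feasibility study, worded as insight and greater understanding, and all four universities are named openly. This stands and limits the weight of the point. It does not remove it, because the article asks a country question and frames the answer by income without saying that two countries rest on one university each.

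A second reply is that an analysis plan could handle it. It could not: the aliasing lies in the choice of sites. It is fair, though, that an article may leave per-university tables and intervals to a fuller document. Their absence here is not the defect; they are part of the remedy.

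A reader might also infer several stronger things that the article does not support:

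- *That the country analysis will report student-level P values or intervals of a known, wrong width.* Data Analysis sets out the P<.05 rule with the paired pre/post test. For country it names only a subgroup analysis in SPSS, which separate within-country pre/post results would also fit.
- *That year mix is wholly confounded with country.* Year of study is recorded, so gains can be stratified by it. Curriculum, topic teaching and local recruitment remain confounded.
- *That the internet requirement does select different kinds of students at each site.* No access figures are given. It is a possible selection and no more.

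**Conclusion.** The point holds. As sited, the study can compare four universities but cannot attribute a difference to country or income level, and the article neither says so nor limits its wording. This follows from the design alone. The main pre/post result within participants is unaffected.

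The numerical size is not known. The ratio of 0.69 to 0.30 rests on an assumed between-university SD, student SD and response. It would be wrong to say flatly that an interval ignoring universities is less than half as wide as it should be: that fails at SD 0.5. The false-positive rates of 13% and 82% likewise rest on assumed ICC and response, and on a student-level test that the article does not name.

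A reader might hope to use the Cork–Galway difference as a yardstick and allow a country claim when another site differs from both Irish sites by more than they differ from each other. The design does not support this. The yardstick has 1 degree of freedom, and passing it would still not separate Mzuzu from Malawi or Fort Hare from South Africa. If the true university means are independent normal draws with no country effect, a given site passes one time in three by symmetry (any of the three pairs is equally likely to be the closest). Requiring twice the gap still lets a site pass 21% of the time.

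**What to change.** 1. Restate research question 2, and the matching text in Data Analysis and in Strengths and Limitations, as a descriptive comparison of the four participating universities.
2. Report the pre/post gain with a 95% CI for each university, showing Cork and Galway separately, stratified by recorded year of study where numbers allow.
3. Draw no conclusion about which country or income setting benefits most.
4. Add to the limitations that Malawi and South Africa are each represented by one university, that Ireland is the only high-income country, and that the internet requirement may have selected respondents.

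The cost is wording and one table from data already collected; no further recruitment is needed. The price is a weaker country statement. A country conclusion would need several universities per country, and an income conclusion would also need more than one high-income country.

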### Conclusions

Results from this study will allow for an investigation into the impact of podcasts in different settings, a high-income country (Ireland), an upper-middle–income country (South Africa), and a low-to-middle–income country (Malawi). The data gathered from this feasibility study will provide more clarity on the potential utility of podcasts as an intervention tool. We will gather data regarding listener demographics (ie, country of residence, age, gender, and year of study) to ascertain the outreach of the podcasts, which could shape future studies on podcasts as an educational tool. If the results of our study are positive in terms of an increase in knowledge and awareness, we hope to identify other populations that might benefit from this sort of educational resource.

## Abbreviations

UCC: University College Cork
WHO: World Health Organization
